### Data Management

All data collected will be coded and be kept strictly confidential. All names will be replaced by unique identifying codes, and the coding matrix will be stored securely and separate from the data itself. All data will be collected and saved on electronic supports and stored on secure servers at the home institutions in Tanzania. The core research team is composed of team members located at IHI and Swiss TPH with different specializations. Data analysis will be done in collaboration, where all the researchers will have access and work on the data as per all collaborative and data management requirement. Any data transfer will take place either over secured networks or in person to a member of the research team. Data will be used for the sole purposes of the research project and published data will not include any kind of information that can be linked to individuals.

### Analytical Methods

By delivering a household survey to the general populations of Kilombero and Same, and an exit survey to people accessing NCD services, we will be able to comparatively analyse the specific challenges and coping mechanisms that people living with NCDs face in accessing services, in relation to the general population.

The data collected from the household survey and exit survey will first be analysed using descriptive statistics to investigate the burden of OOPs and economic losses associated with living with hypertension and/or diabetes, and to determine how much households spend upon the direct and indirect costs of accessing NCD care. General hypotheses related to the geographic and economic accessibility of health care, such as whether distance from a health facility is associated with direct and indirect healthcare costs, and whether distance from a health facility moderates the association between social health protection and household health expenditure, will be explored using linear mixed models and analyses of variance.

We will quantify the proportion of the household survey respondents who were hypertensive or diabetic, and not aware of their condition or not enrolled in care. We will then use univariate and multivariate logistic regression analyses to identify differences between the household respondents with an NCD who are not enrolled in care and NCD patients from the exit interviews who are enrolled in care. We will quantify systematic and individual characteristic predictors of willingness-to-pay for NCD care and social health protection schemes for people in care for non-NCD reasons, for NCD reasons, and household respondents.

A regression model will then be used to assess whether living with hypertension and/or diabetes is associated with financial hardship, and/or illness-related economic and productivity losses, using the indicators catastrophic health expenditure and impoverishment. An analysis of variance (ANOVA) of mean spending by revenue source will then be used to determine the relative importance of financial contributions from various household revenue streams to covering the costs of NCD care, such as:

- Earnings from work (informal or formal)

- Selling personal property (clothing, bicycle, furniture, etc.)

- Financial contributions from the social network (friends, family, neighbours, etc.)

- Other means of support from the social network, such as accompaniment to the health facility, or offering transport to the health facility

- Social health protection, or other forms of social protection (CHF, NHIF, TASAF, etc.)

Egocentric social network analysis will then be used to analyse and visualise the network of actors and individuals that support people living with NCDs, and to characterise and quantify the function of a patient’s support network. Similar in concept to the more typical sociocentric social network analysis, egocentric social network analysis instead will analyse the composition and function of a network of actors in relation to a single entity; in this case, an individual with hypertension and/or diabetes). The main units of the egocentric social network analysis will be the composition of the patient’s support network (type of relationship, propinquity, age, gender, etc.), and the type of social support that is being received and provided (cash, personal care, clothing, etc.). The questionnaire instrument relevant to the proposed study has been included in this IRB submission package.

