### Study Design

This study will use primary data that will be collected in two surveys: A general household survey including biometric testing for hypertension and diabetes, and an exit questionnaire administered to patients following their visit at a health facility.

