### Sampling Strategy and Sample Size

#### *Household survey*

We will conduct a household survey to collect information on household demographic and economic characteristics, health insurance and social protection, chronic illness, healthcare access and utilisation, household health expenditure, out of pocket payments for health care, and coping strategies to deal with diseases. In order to answer the key research question, information will be collected regarding direct and indirect household out-of-pocket expenditure (OOPs) on healthcare, how the household pays for their OOPs or social health protection premiums, economic productivity loss due to illness, recent healthcare utilisation, and the role of one’s social network in coping with illness. For respondents that accept, we will also measure blood pressure and random blood sugar to quantify undiagnosed and untreated hypertension and possible diabetes in the population. We will counsel patients with results outside of the normal range of the importance of following up with a healthcare provider to formally diagnose and initiate treatment if needed.

Using a stratified sampling approach, a household survey will be delivered throughout Kilombero and Same districts. In order to detect associations with the primary outcome of household health expenditure (power of 0.80, significance level of 0.05), a minimum sample size of 202 households per district is required. To calculate the minimum sample size, a household health expenditure of 30,000 Tanzanian shillings was used as a benchmark; corresponding to the cost of enrolling a household in the iCHF. However, in order to also answer research questions associated with our secondary objectives, we will seek a total sample size of 390 households per district.

As such, in each of Kilombero and Same district, 15 households from each district’s only town (Ifakara and Same, respectively), and 15 households from a random selection of 25 other villages will be sampled (Table 1).

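### Unconfirmed household screening results are analysed as disease, so screening false positives can enter only the not-in-care side of the logistic comparison

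*Protocol*

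**What the plan says.** The Study Design section describes two instruments: "A general household survey including biometric testing for hypertension and diabetes, and an exit questionnaire administered to patients following their visit at a health facility". Biometric testing is attached to the first only.

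The Household survey section says that, in respondents who accept, staff will "measure blood pressure and random blood sugar to quantify undiagnosed and untreated hypertension and possible diabetes in the population". People with abnormal results are counselled on "following up with a healthcare provider to formally diagnose and initiate treatment if needed". No return visit or confirmatory test by the study is described.

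The Analytical Methods section first quantifies the household respondents "who were hypertensive or diabetic, and not aware of their condition or not enrolled in care". It then uses univariate and multivariate logistic regression to identify "differences between the household respondents with an NCD who are not enrolled in care" and NCD patients in care from the exit interviews. Research Question 2 gives the purpose: to find the undiagnosed and undertreated proportion, and the barriers that separate these people from patients who do reach care.

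**The concern.** By the protocol's own account, an abnormal household reading is a reason to seek a diagnosis and is not itself a diagnosis. For diabetes the Household survey section adds the qualifier *possible*. The analysis text drops this caution. A respondent who is unaware of the condition can be found only through the household test, so the unaware part of the group consists of unconfirmed screen-positives.

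The two sides of the regression are also ascertained differently. The natural reading of the Analytical Methods section is that the not-in-care side pools respondents already diagnosed but out of care with respondents flagged only by the test. The in-care side consists of patients found through NCD care. A screening false positive can join the first group but not the second. Characteristics that go with not having persistent disease could then be reported as barriers to care, which is what Research Question 2 sets out to measure.

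**Working it through.** The protocol states no figure for screening accuracy, so there is none to reproduce. The check has three parts.

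**1. Blood pressure: how many positives are not persistent?**

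Inputs from the protocol: hypertension prevalence 19.9% (note to Table 1) and 390 households per district (Household survey), so 2 × 390 = 780. Table 1 prints 790, but its own strata give 2 × (15 + 25 × 15) = 780.

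Assumptions: 19.9% is the share above threshold on one occasion, one tested respondent per household, all accept testing, total SD S = 18-22 mmHg, within-person SD w = 7-10 mmHg, normal distributions.

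- The standard normal value exceeded by 19.9% is z = 0.845.
- The SD of usual values is b = √(S² − w²). The true share above threshold is P(Z > zS/b).
- The correlation of a reading with the usual value is b/S. The share above threshold on both follows from the bivariate normal distribution.

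Worked case, S = 20 and w = 8: b = √(400 − 64) = 18.33, zS/b = 0.922, true prevalence 17.8%. False-positive share of positives: 0.278. Ratio of apparent to true: 19.9/17.8 = 1.12.

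| S | w | False-positive share | True prevalence | Apparent/true | False positives per 780 | False negatives per 780 |
|---|---|---|---|---|---|---|
| 22 | 7 | 0.211 | 18.6% | 1.07 | 33 | 23 |
| 20 | 8 | 0.278 | 17.8% | 1.12 | 43 | 27 |
| 18 | 10 | 0.426 | 15.5% | 1.29 | 66 | 32 |

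Among 780 × 0.199 = 155 positives, gross false positives are about 33 to 66. Net of false negatives, the excess is about 10 to 35 people. The net figure is the one that bears on prevalence. The gross share bears on who is in the regression group.

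**2. Is the direction of bias in the undiagnosed proportion certain?**

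With sensitivity Se, specificity Sp, prevalence p and undiagnosed share u, apparent undiagnosed = Se·u + (1 − Sp)(1 − p). All accuracy values here are assumed.

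- Hypertension, p = 0.199, 30% already diagnosed (u = 0.139, about 109 of 780): Se 0.90 and Sp 0.90 gives 160 flagged (1.48-fold, 39% false positive). Se 0.80 and Sp 0.98 gives 99 flagged (0.92-fold, 13% false positive). Over Se 0.70-1.00, Sp 0.85-0.98 and 0-50% already diagnosed, the ratio runs from 0.78 to 2.21.
- Diabetes, assumed 3-10% undiagnosed, Se 0.4-0.8, Sp 0.95-0.995 (all others taken as non-cases): the ratio runs from 0.45 to 2.42.

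**3. What does one-sided misclassification do to the regression?**

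Example with assumed values: a covariate is present in 50% of in-care patients and 25% of people truly out of care, so the true odds ratio is (0.50/0.50)/(0.25/0.75) = 3.0. Let 40% of the not-in-care group be false positives.

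- Covariate prevalence 40% in the false positives: 0.6 × 0.25 + 0.4 × 0.40 = 0.31, and the odds ratio is 0.69/0.31 = 2.23.
- Covariate prevalence 25%: the odds ratio stays 3.0.
- Covariate prevalence 10%: 0.6 × 0.25 + 0.4 × 0.10 = 0.19, and the odds ratio is 0.81/0.19 = 4.26.

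The bias can go either way, depending on how false positives differ from true cases.

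**The case against.** The strongest reply is that the text is less specific than the concern needs. Four parts of it stand.

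- The Household survey section attaches *possible* to diabetes only, and the advice to seek formal diagnosis is a statement about participants' care. For hypertension the two sections do not flatly contradict each other. The weakness is that the analysis carries no trace of the unconfirmed status.
- The regression group is not made up of screen-positives alone. It includes respondents who know their diagnosis and are out of care, since the survey also collects chronic illness and use of care. The size of the screened-only part is unknown.
- A single visit is an inference from the absence of any described revisit. Cut-offs and number of readings are not given, but an analysis plan or the separately submitted questionnaire may hold them, so their absence is no finding.
- The 155 positives rest on a total prevalence, not an undiagnosed one, and 780 tested is an upper bound because testing is voluntary.

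A reader might infer that the plan certainly overstates undiagnosed disease. The documents do not support that. False negatives offset part of the excess for blood pressure, and random glucose may miss enough true cases to reverse the direction. A reader might also infer that diagnosed-not-in-care respondents should become the main comparison. That would push aside the undiagnosed, whom Research Question 2 names as a target.

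The reply does not remove the asymmetry: the stated test is in one survey only, and it feeds one side of the comparison only.

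**Conclusion.** The point holds in a limited form. Household readings that the protocol regards as awaiting diagnosis are analysed as disease, and the resulting false positives can enter only the not-in-care group. For blood pressure, under the SDs assumed above and with 19.9% read as a one-occasion rate, 21-43% of positives have a usual value below the threshold and net prevalence is overstated about 1.07- to 1.29-fold. Other accuracy assumptions can give understatement, and for random glucose the net direction is open. The effect on the odds ratios cannot be signed in advance. The issue touches Research Question 2 and not the primary outcome, household health expenditure. It is worth correcting because the correction is cheap.

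**What to change.** In the Analytical Methods section:

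1. Report the household result as *raised blood pressure / raised random glucose at screening (unconfirmed)*, not as hypertension or diabetes of which the respondent is unaware.
2. Split the not-in-care group into previously diagnosed respondents and newly screen-positive respondents.
3. Report the logistic comparison with in-care exit patients separately for each subgroup. State the previously diagnosed comparison as a sensitivity analysis, with the same self-reported-diagnosis definition in both surveys.

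The household survey is already set to collect chronic illness and use of care, and the Exit survey section says most questions are shared, so little or no new data collection should be needed. The cost is that each subgroup is smaller and its estimates less precise.

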# Research for development (R4D): Health systems governance for an inclusive and sustainable social health protection in Ghana and Tanzania - Phase 2; Sub Study: Implementation of health financing policy and social health protection schemes in Tanzania

## Executive Summary

The Ifakara Health Institute, in collaboration with the Swiss Tropical and Public Health Institute, is seeking ethical clearance for the below protocol investigating the accessibility of NCD care in Tanzania, as a sub-study in the second phase of the Research for Development (R4D): Health systems governance for an inclusive and sustainable social health protection in Ghana and Tanzaia. Chronic non-communicable diseases (NCD), especially cardio-metabolic disorders such as hypertension and diabetes, are on the rise in sub-Saharan Africa. However, health systems in sub-Saharan Africa are mainly equipped for acute episodic treatment, and as such are ill-equipped for the successful treatment of non-communicable, chronic conditions. As such, the objectives of this protocol are to explore the implementation of health financing strategies particularly related to geographic accessibility of NCD care, economic barriers, willingness to pay for access to chronic disease care, and engagement in chronic care. This protocol will utilise both secondary and primary data to meet these objectives, and will begin by analysing secondary data provided by the National Health Insurance fund in order to provide an overview of NCD care provision in Tanzania and build a geospatial model of NCD care accessibility across Tanzania. Primary data will then be collected by recruiting households and patients to participate in surveys in order to better understand the costs of accessing NCD care, predictors of disengagement from care, and the willingness-to-pay for NCD care. Quantifying patient access and utilization of NCD care in Tanzania will provide crucial evidence for health systems strengthening efforts to provide NCD care in Tanzania, the importance of which will only increase as the burden of NCDs continues to rise due to demographic changes and urbanisation. In doing so, this study seeks to improve the equity of access to chronic care and inform the improvement of health financing policy and implementation so that Tanzania may work towards achieving a more inclusive, sustainable, and equitable health system and social health protection system.

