The second research question will aim to quantify the direct and indirect cost associated with accessing NCD care services, and describe strategies for coping with the cost burden. This includes determining which support systems people living with NCDs utilise, including their social networks, to cope with these costs. It will also seek to determine the cost of not having social health protection by comparing the total costs incurred between NHIF beneficiaries, iCHF beneficiaries, and those who are not part of a social health protection scheme. The role of patient social networks will be especially important to investigate, as it has been reported that people often attempt to capitalise on their social networks to avoid out-of-pocket expenditure (OOPs) by being added to another household’s iCHF membership, or by borrowing money from their social network [8]. Furthermore, this objective will take into account that although beneficiaries of social health protection may be less likely to experience financial hardship due to the direct cost of their illness, their illness may still impose a social and economic burden in the form of missed work days and lost income for either the individual living with the NCD, or their caregiver at times when one’s illness prevents them from working [9].

### Research Question 2

The third research question aims to understand the differences between people with NCDs who are engaged in care and those that are not. We aim to identify the proportion of the population that remains undiagnosed, and undertreated for hypertension and diabetes, and the barriers or perceived barriers to appropriately utilising NCD treatment compared with the patients who are accessing NCD care. In addition to socio-demographic and geographic mediators of care utilisation, we will quantify the willingness-to-pay for chronic disease care under different payment options, specifically out-of-pocket payments versus the payment of health insurance premiums, for both patients and individuals in the community.

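### The single in-care versus not-in-care logistic model pools people unaware of their condition with people who know and do not attend, so it does not isolate disengagement or barriers to treatment

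*Protocol*

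**What the plan says.** Under Sampling Strategy and Sample Size (Household survey), respondents who agree have their blood pressure and a random glucose reading taken, so that undiagnosed and untreated disease can be counted. Analytical Methods then has two steps.

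- **Descriptive step.** It quantifies household respondents who are "hypertensive or diabetic, and not aware of their condition or not enrolled in care".
- **Model.** It uses "univariate and multivariate logistic regression analyses to identify differences" between "household respondents with an NCD who are not enrolled in care" and "NCD patients from the exit interviews who are enrolled in care".

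Three statements of purpose bear on this comparison.

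- The second listed objective (Objectives and Research Aims) is broad: how people with NCDs who are engaged in care differ from those who are not.
- Research Question 2 asks to "identify the proportion of the population that remains undiagnosed, and undertreated for hypertension and diabetes" and to find "the barriers or perceived barriers to appropriately utilising NCD treatment compared with the patients who are accessing NCD care".
- The Executive Summary says the surveys are meant to show "predictors of disengagement from care".

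**The concern.** Hypertension and diabetes can be present without the person knowing, and the household survey is designed to find such cases. Someone whose raised reading is first found on the survey day is necessarily not enrolled in care. In the model, that person gets the same outcome code as someone who was diagnosed and does not attend.

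The two states can have different causes. Not being diagnosed may reflect no contact with screening. Not attending after diagnosis may reflect cost, distance or dissatisfaction. An unaware person has not left care and cannot describe obstacles to treating a condition that he or she does not know about.

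At stake is the policy reading. A pooled odds ratio does not tell the reader whether the finding argues for cheaper or closer treatment or for more screening. A real barrier among diagnosed people can also look weaker than it is.

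**Working it through.** The protocol gives no sample size, power or expected effect for this regression, so there is no figure of its own to reproduce. The check covers who falls in the group, what the pooled odds ratio estimates, and how many people a split would leave.

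**1. Who is in the not-in-care group**

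- Household respondents can be classed as having an NCD from survey-day testing (Household survey).
- The sentence just before the model counts people unaware of their condition (Analytical Methods).
- The model's household group is defined only by having an NCD and not being enrolled. It has no awareness condition.
- No other section restricts the model to diagnosed people or adds a diagnosis stage.

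**2. What the pooled odds ratio estimates**

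Let U, A and C be the counts of unaware, aware but not in care, and in care. Subscript 1 means exposed to a factor and 0 means unexposed.

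- OR_U = U1·C0 / (U0·C1) and OR_A = A1·C0 / (A0·C1)
- Pooled OR = (U1 + A1)·C0 / [(U0 + A0)·C1] = p·OR_U + (1 − p)·OR_A, where p = U0 / (U0 + A0)

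The crude pooled odds ratio is thus exactly a weighted average, with p the unaware share among the unexposed people not in care. The protocol does not give p. With assumed values of 0.6 and 0.8:

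| OR_A (aware, not in care) | OR_U (unaware) | p = 0.6 | p = 0.8 |
|---|---|---|---|
| 2.0 | 1.0 | 0.6×1.0 + 0.4×2.0 = 1.4 | 0.8×1.0 + 0.2×2.0 = 1.2 |
| 2.0 | 0.5 | 0.6×0.5 + 0.4×2.0 = 1.1 | 0.8×0.5 + 0.2×2.0 = 0.8 |

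**3. The same check with the unaware share u taken over the whole not-in-care group**

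Assume 30% exposure among patients in care and OR_A = 2.5. Exposure odds in care are 0.3/0.7 = 0.4286. Among aware people not in care they are 2.5 × 0.4286 = 1.0714, a prevalence of 0.517. Exposure prevalence in the merged group is u·P_U + (1 − u)·P_A.

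For OR_U = 1.0 and u = 0.5, this is 0.5×0.300 + 0.5×0.517 = 0.409. The odds are 0.691, and the merged OR is 0.691/0.4286 = 1.61. The full set is:

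| OR_U | u = 25% | u = 50% | u = 75% | u = 90% |
|---|---|---|---|---|
| 1.0 | 2.01 | 1.61 | 1.28 | 1.11 |
| 0.5 | 1.78 | 1.24 | 0.83 | 0.62 |
| 2.5 | 2.50 | 2.50 | 2.50 | 2.50 |

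The merged estimate equals the odds ratio for aware people only when the factor acts equally at both stages.

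**4. Numbers left after a split**

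- Households: 2 × (15 + 25×15) = 780, which agrees with 390 per district (the printed Table 1 total is 790).
- Hypertension prevalence in Table 1: 19.9% (95% CI 17.1–22.9).
- Expected hypertensive respondents, assuming one tested person per household and full acceptance: 780 × 0.199 ≈ 155 (133 to 179 over the interval).
- Not in care, at assumed shares of 50–90%: about 78 to 140.
- Aware but not in care, if 25–90% of those are unaware (assumed): from 155.2×0.5×0.10 ≈ 8 to 155.2×0.9×0.75 ≈ 105.

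Diabetes without hypertension would add to these counts.

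**The case against.** **The merging is inferred.** The model sentence does not repeat the words about awareness. Having an NCD could mean a known NCD, since the protocol treats a raised glucose reading only as possible diabetes and leaves diagnosis to a provider. Outcome coding could also be settled in an analysis plan that is not at hand. This has some force. But the protocol itself names both groups and the model, directly after a count that includes unaware people. If only known disease was meant, a short clarification is still needed.

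**The broad objective is met.** This stands. The pooled contrast does compare engaged with not engaged, and distance, cost and insurance affect undiagnosed people too. A reader might infer that the model cannot say anything about objective 2; the documents do not support that. The gap concerns disengagement and perceived barriers to treatment.

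**Disengagement is a thin basis.** The word is in the Executive Summary, and neither the objectives nor Analytical Methods takes it up. That is fair, but the barriers wording in Research Question 2 carries the point without it.

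**The descriptive sentence may mean two quantities.** This stands. A reader might take it as one combined proportion, but the text does not settle this, and Research Question 2 names the undiagnosed and the undertreated separately. The point rests on the model sentence.

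**The sizes are hypothetical.** This also stands. A reader might infer from the second row of the first table that barriers will vanish or reverse, or that results will mainly reflect lack of diagnosis. The protocol names no factor with opposite effects and gives no unaware share.

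**Conclusion.** The concern holds in a limited form. Followed as written, the model pools unaware people with aware non-attenders. It answers the broad objective but does not isolate predictors of disengagement or perceived barriers to treatment.

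That the pooled odds ratio is a weighted average follows from algebra. The degree of dilution does not come from the protocol: 2.0 falling to 1.4–1.2 rests on an assumed 60–80% unaware among the unexposed not in care and on no association between the factor and being unaware. With equal effects at both stages there is no distortion.

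The problem lies in the specified analysis, not in the data. The descriptive step already needs both awareness and enrolment, so the analysis can be repaired.

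**What to change.** In Analytical Methods:

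1. Report separately the proportion unaware and the proportion aware but not in care.
2. Replace the binary outcome with three states (unaware, aware but not in care, in care) in a multinomial logistic model. Alternatively, fit two models: unaware versus aware, and not in care versus in care among aware people.
3. If two models are used, fit unaware versus aware within the household sample only. Adding facility patients would make the aware group a blend of two samples in proportions set by recruitment targets.
4. Base conclusions on treatment barriers and disengagement on the aware-only contrast, and word them as associations with current care status, because the surveys are cross-sectional.
5. Keep the merged contrast, if wanted, as a secondary summary for the broad objective.

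This changes analysis wording only. The cost is precision. The aware-but-not-in-care group may be small (about 8 to 105 hypertensive respondents under the assumed shares above), so intervals will be wider. At the low end, the number of covariates would have to be limited.
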